## Abstract

**Background:**

For most tubal ectopic pregnancies (EP) surgery is the treatment of first choice. Whether surgical treatment should be performed conservatively (salpingostomy) or radically (salpingectomy) in women wishing to preserve their reproductive capacity, is subject to debate. Salpingostomy preserves the tube, but bears the risks of both persistent trophoblast and repeat ipsilateral tubal EP. Salpingectomy, avoids these risks, but leaves only one tube for reproductive capacity. This study aims to reveal the trade-off between both surgical options: whether the potential advantage of salpingostomy, i.e. a better fertility prognosis as compared to salpingectomy, outweighs the potential disadvantages, i.e. persistent trophoblast and an increased risk for a repeat EP.

**Methods/Design:**

International multi centre randomised controlled trial comparing salpingostomy versus salpingectomy in women with a tubal EP without contra lateral tubal pathology. Hemodynamically stable women with a presumptive diagnosis of tubal EP, scheduled for surgery, are eligible for inclusion. Patients pregnant after in vitro fertilisation (IVF) and/or known documented tubal pathology are excluded. At surgery, a tubal EP must be confirmed. Only women with a tubal EP amenable to both interventions and a healthy contra lateral tube are included. Salpingostomy and salpingectomy are performed according to standard procedures of participating hospitals. Up to 36 months after surgery, women will be contacted to assess their fertility status at six months intervals starting form the day of the operation.

The primary outcome measure is the occurrence of spontaneous viable intra uterine pregnancy. Secondary outcome measures are persistent trophoblast, repeat EP, all pregnancies including those resulting from IVF and financial costs. The analysis will be performed according to the intention to treat principle. A cost-effectiveness analysis will be performed within a decision analysis framework, based on costs per live birth, including IVF treatment whenever a spontaneous pregnancy does not occur. Patients' preferences will be assessed using a discrete choice experiment.

**Discussion:**

This trial will provide evidence on the trade off between salpingostomy and salpingectomy for tubal EP in view of the pros and cons of both interventions and will offer guidance to clinicians in making the right treatment choice.

**Trial registration:**

Current Controlled Trials ISRCTN37002267

## Background

In the treatment of tubal ectopic pregnancy (EP), laparoscopic surgery remains the cornerstone of treatment [1]. In the absence of randomised data, the question as to whether surgical treatment should be performed either conservatively (salpingostomy) or radically (salpingectomy) in women with desire for future pregnancy is subject to ongoing debate.

Since the first study demonstrated the potential effectiveness of salpingostomy, this treatment has been compared with salpingectomy in numerous non-randomised studies [2]. Pooled data showed no beneficial effect of salpingostomy on intra uterine pregnancy (IUP) whereas there is an increased risk of repeat EP [3,4]. Based on these findings, the Royal College of Obstetricians and Gynaecologists guideline advises salpingectomy as the preferred standard surgical approach for tubal EP [5]. However, there are good reasons to question this advice. Interpretation of the pooled data is troublesome since many of the original studies failed to report essential details, e.g. time to pregnancy, presence of the desire for future pregnancy and whether subsequent pregnancies occurred either spontaneously or after fertility treatment, such as in vitro fertilization (IVF). Only a few non-randomised studies have taken these matters into account and came to different conclusions [6-11]; The IUP rates were higher and the time to an IUP was shorter after salpingostomy compared to salpingectomy. Especially in women with a history of bilateral tubal pathology, salpingostomy offered better IUP rates than salpingectomy, albeit at the cost of an increased risk for repeat EP [6-8,10]. In women without a history of tubal pathology this benefit was less clear and also in these women there was an increased risk for repeat EP [8]. In view of these data, we feel that the most effective type of surgery for women with a tubal EP in the presence of contra lateral tubal pathology with desire for future pregnancy is salpingostomy. In women without contra lateral tubal pathology, the most optimal surgical treatment is currently unknown.

### Objective

To study whether the potential advantage of salpingostomy, i.e. a better fertility prognosis as compared to salpingectomy, outweighs the potential disadvantages of this treatment, i.e. persistent trophoblast and an increased risk for repeat EP in women with a tubal EP without contra lateral tubal pathology.

## Methods

### Participating centres

This study is an international multi centre randomised controlled trial, originally in a Dutch-Swedish-British collaboration since October 1^st^, 2005. During the study period, other centres were contacted to participate. Since June 1^st^, 2006, a centre in North Carolina (USA) has joined the collaboration.

### Inclusion criteria

Hemodynamically stable women ≥ 18 years of age with a presumptive diagnosis of tubal EP who are scheduled for surgery, are eligible for the trial. Excluded are women without desire for future pregnancy, patients pregnant after IVF, patients with a pregnancy in a solitary tube and those patients with a contra lateral tubal occlusion or hydrosalpinx as documented earlier at hysterosalpingography or laparoscopy or as found during surgery for the index EP.

### Ethical considerations

Approval for this study was obtained from the Medical Ethical Committees of the Academic Medical Centre, Amsterdam, The Netherlands, Sahlgrenska University Hospital, Göteborg, Sweden, Kings Hospital, London, UK, and Wake Forest University School of Medicine, Winston-Salem, North Carolina, USA.A quality assessment has been made and approved by three external referees, experts from the field by the Netherlands Organization for Health Research and Development (ZonMw).

In each patient fulfilling the inclusion criteria, written informed consent is obtained before randomisation. Women refusing participation are registered.

### Randomisation

Randomisation is performed during surgery by accessing a central internet-based randomisation program. Randomisation is stratified for hospital, patient's age and history of tubal pathology (i.e., previous EP, previous tubal surgery, and previous pelvic inflammatory disease).

### Interventions

At surgery, which can either be performed laparoscopically or by laparotomy, the presence of a tubal EP must be confirmed. Patients with tubal rupture will be excluded, whenever this interferes with the possibility to perform salpingostomy. The surgeon will assess the status of the contra lateral tube during the procedure. If, according to the surgeon, the condition of the contra lateral tube renders future pregnancy unlikely in case the patient will be randomised to salpingectomy for the index tubal pregnancy (i.e., hydrosalpinx, severe peritubal adhesions, malformations, or other reasons), the patient is excluded. Thus, only patients with a tubal EP that allows both interventions, and a contra lateral tube that would allow spontaneous conception in case of salpingectomy, are being included in the study.

Whenever necessary, laparoscopy may be converted to open surgery. Salpingostomy is performed following local procedural standards used in the participating hospitals. Preferably linear salpingostomy is performed, but other methods are allowed. Whenever necessary, salpingostomy may be converted to salpingectomy, e.g. in case of uncontrollable bleeding. A complete salpingectomy is performed following local procedural standards of the participating hospitals. All methods of treatment are registered in the Case Record Form.

### Follow-up

#### Short term follow-up

Complications during the immediate postoperative period are registered in the Case Record Form. To identify persistent trophoblast in both treatment groups, serum hCG is measured postoperatively on a weekly basis until undetectable in both treatment arms to identify persistent trophoblast. Serum hCG concentrations are expressed in IU/L (conversion factor to SI unit, 1.00 according to the World Health Organization Third International Standard 75/537). Persistent trophoblast is defined as post operative rising or plateauing serum hCG concentrations [12].

#### Long term follow-up

To assess fertility after the operation of the index tubal EP, the patients are contacted by means of a questionnaire, every six months for a period of 36 months. The questionnaire focuses on the presence of a desire for pregnancy, unprotected sexual intercourse with a chance of spontaneous conception, contraceptive use, infertility treatment, and the occurrence of any pregnancies and their outcomes (Figure 1).

**Figure 1 F1:**
[figure not shown]
Flowchart ESEP study.

### Outcome measures

#### Primary outcome measure

The primary outcome measure is the time to the occurrence of a spontaneous viable IUP. A viable IUP is defined as a pregnancy visible at ultrasound at a gestational age of ≥ 12 weeks with fetal cardiac activity, or the delivery of a child. If an IUP does not occur, follow-up ends on the day of the last consultation.

#### Secondary outcome measures

Secondary outcome measures are persistent trophoblast, repeat EP, all pregnancies including those resulting from IVF and financial costs. Patients' preferences will also be assessed.

Persistent trophoblast is defined as rising or plateauing serum hCG concentrations postoperatively and is primarily treated with systemic methotrexate (MTX) or otherwise if necessary [12].

Repeat EP is defined as a visible EP at ultrasound, a pregnancy of unknown location (PUL) with a serum hCG above the discriminatory zone or as a persisting PUL for which surgical or medical treatment with MTX is installed. Failing PULs, which are managed expectantly with an uneventful decline of serum hCG to an undetectable level, will be reported separately and are not considered repeat EPs. The date of occurrence of an EP or failing PUL will also be determined from the first day of the last menstrual period.

Costs are expressed as direct costs, for which data on both costs and used resources are assessed in a subset of the participating hospitals.

Patients' preferences are assessed by an online questionnaire using a discrete choice experiment (DCE) based on characteristics of both interventions and will be compared with a control group, recruited among women visiting the infertility clinics in a subset of the participating hospitals.

### Statistical analysis

The analysis is performed according to the *intention to treat *principle. Short term outcome measures are expressed in RR and their 95% confidence intervals.

Future fertility is assessed by means of life table analysis. Kaplan-Meier curves are constructed, estimating the cumulative probability of spontaneous IUP and repeat EP over time. The assessment of fertility status is censored for those periods when women used contraceptives or did not have sexual intercourse. In case a spontaneous viable IUP does not occur, follow up ends at the last date of consultation, or at the moment when either IVF or tubal surgery is performed. Spontaneous conceptions that occur after failed IVF treatment will be registered, but these pregnancies will not be considered as endpoint in the analysis. The log-rank test is used to test differences between the Kaplan-Meier curves for statistical significance. The differences between both treatment modalities are expressed as a FRR with 95% confidence interval, calculated through Cox proportional hazard analysis.

A cost-effectiveness analysis will be performed within a decision analysis framework, based on outcome of costs per live birth, including IVF programs in case a spontaneous pregnancy does not occur.

Patient's preferences will be analysed by differences in outcome of the DCE.

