### Sample size

The IUP rate after salpingectomy is assumed to be 40% after 36 months and the median time to pregnancy in this group is 1.4 year [8]. We consider an increase of the IUP rate by 10–15% after salpingostomy compared to salpingectomy clinically relevant to overcome the disadvantages of persistent trophoblast and repeat EP. In order to prove a reduction of the median time to pregnancy from 1.4 year to 1 year, 225 patients in each group are required (significance level of 5%, a power of 80%, and 5% loss to follow up in both groups, 2-sided test).

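### The RR is the only effect measure stated for persistent trophoblast, although few or no events are expected after salpingectomy; a risk difference should be reported beside it

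*Protocol article*

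**What the plan says.** The Statistical analysis section gives one sentence on short-term outcomes: "Short term outcome measures are expressed in RR and their 95% confidence intervals". Persistent trophoblast falls under it. Short term follow-up states: "To identify persistent trophoblast in both treatment groups, serum hCG is measured postoperatively on a weekly basis", and the outcome is listed first among the secondary outcomes.

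The Abstract's Background expects a marked difference between the arms. Of one operation it says: "Salpingostomy preserves the tube, but bears the risks of both persistent trophoblast and repeat ipsilateral tubal EP". Of the other it says: "Salpingectomy, avoids these risks, but leaves only one tube for reproductive capacity". No rate is given for either arm.

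The harm matters to the objective, which asks whether better fertility prospects outweigh persistent trophoblast and repeat ectopic pregnancy. The Sample size section sets a gain of 10–15% in the intrauterine pregnancy (IUP) rate as "clinically relevant to overcome the disadvantages of persistent trophoblast and repeat EP". The Discussion adds that the number of cases prevented could decide the matter if salpingostomy proves no better.

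**The concern.** A ratio works poorly when the authors expect its denominator to be close to zero. The Sample size section compares salpingostomy with salpingectomy, so salpingectomy is the natural reference. With one or two events there, the RR has a very wide interval and shifts greatly when a single event is added or removed. With none, it cannot be computed.

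Intention to treat gives little protection. The conversion that the Interventions section describes runs one way: "Whenever necessary, salpingostomy may be converted to salpingectomy, e.g. in case of uncontrollable bleeding". It adds no women with a conserved tube to the salpingectomy arm.

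The scale is the second difficulty. The gain is stated as a change in a rate and the harm is discussed as a number of cases, but the stated measure of the harm is a ratio. An RR of 16 cannot be set against extra pregnancies per 100 women, whereas about 7 extra cases per 100 can.

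**Working it through.** **Inputs.** The article states no rate, RR or precision for persistent trophoblast, so there is no figure of its own to reproduce. The one figure used is the denominator: "225 patients in each group are required". It was set for time to pregnancy and is taken here as given. All event rates are assumptions: about 2% to 20% after salpingostomy, with 7% as the main example (0.07 × 225 = 15.75, or 16 events), and 0% to 2% after salpingectomy.

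**Chance of no salpingectomy events.** P(0) = (1 − p)^225.

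- p = 0.2%: 0.998^225 = 0.637
- p = 0.5%: 0.995^225 = 0.324
- p = 1%: 0.99^225 = 0.104
- p = 2%: 0.98^225 = 0.011

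P(0) exceeds one half only when p is below 1 − 0.5^(1/225) = 0.0031, about 0.3%. After the planned 5% loss (0.95 × 225, about 214 women) the 0.5% and 1% figures rise slightly, to 0.342 and 0.116.

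**RR and its interval.** RR = a/b with equal arms, and SE(log RR) = √(1/a − 1/225 + 1/b − 1/225).

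For 16 v 1: SE = √(0.0625 + 1 − 0.0089) = 1.026 and exp(1.96 × 1.026) = 7.48. The limits are 16/7.48 = 2.1 and 16 × 7.48 = 120. For zero events, 0.5 is added to each arm's event count and to its total.

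**Risk difference and its interval (Newcombe).** For 16 v 1 the Wilson limits are 4.42% to 11.24% around 7.11%, and 0.08% to 2.47% around 0.44%. The difference is 6.67 points.

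- Lower limit: 6.67 − √((7.11 − 4.42)² + (2.47 − 0.44)²) = 3.3
- Upper limit: 6.67 + √((11.24 − 7.11)² + (0.44 − 0.08)²) = 10.8

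**Results over the assumed range.**

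| Events, salpingostomy v salpingectomy | RR (95% CI) | Risk difference, points (95% CI) |
|---|---|---|
| 4 v 1 | 4.0 (0.45 to 35.5) | 1.3 (−1.0 to 4.1) |
| 9 v 0 | undefined; 19 (1.1 to 325) with 0.5 added | 4.0 (1.5 to 7.4) |
| 9 v 2 | 4.5 (0.98 to 20.6) | 3.1 (0.1 to 6.6) |
| 16 v 0 | undefined; 33 (2.0 to 547) with 0.5 added | 7.1 (3.9 to 11.2) |
| 16 v 1 | 16 (2.1 to 120) | 6.7 (3.3 to 10.8) |
| 16 v 2 | 8.0 (1.9 to 34) | 6.2 (2.7 to 10.4) |
| 16 v 4 | 4.0 (1.4 to 11.8) | 5.3 (1.5 to 9.6) |
| 45 v 1 | 45 (6.3 to 324) | 19.6 (14.4 to 25.3) |
| 45 v 4 | 11.2 (4.1 to 31) | 18.2 (12.8 to 24.0) |

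With 16 salpingostomy events, going from 0 to 1 to 2 salpingectomy events takes the RR from undefined to 16 to 8. The risk difference moves by 2/225, or 0.9 points. The RR limits differ by a factor of about 56 for 16 v 1 and about 18 for 16 v 2.

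**The case against.** The RR is a conventional and valid measure for a binary outcome. This is a condensed article, and a supplementary risk difference, an interval method or a zero-cell rule could well stand in a full protocol or SAP that is not shown. That stands against any complaint that such details are missing. It does not remove the point that the article itself chooses a measure ill suited to what it expects.

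A reader might go further and infer four things that the document does not support.

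- *That the RR is to be the sole report.* The text does not say so, and it does not rule out counts or percentages by arm.
- *That the RR will probably be undefined.* This needs a salpingectomy risk below about 0.3%, and no rate is stated. Weekly hCG in both arms suggests that the authors do not treat the risk as nil. The direction of the ratio is not stated either; inverted, zero salpingectomy events give an RR of 0, although the log-based interval still fails.
- *That the RR would be uninformative.* With 16 v 0 (0.5 added), 16 v 1 and 16 v 2 the lower limit is about 2, so direction and a lower bound are clear. What is poorly known is the size.
- *That the harm cannot enter the trade-off.* Arm-level risks can go straight into the planned decision analysis, and the discrete choice experiment is another route. The counts needed for an RR also yield the risk difference.

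**Conclusion.** The point holds as a matter of choosing the better measure. For persistent trophoblast, the one stated effect measure is very imprecise when salpingectomy events are few, is undefined against that arm when there are none, and is not on the scale on which the article frames benefit and harm. On an assumed 7% after salpingostomy, the same data give an RR interval of 2.1 to 120 but a risk difference known to within about 4 points either way. The chance of an undefined RR runs from 64% at an assumed salpingectomy risk of 0.2% to 10% at 1% and 1% at 2%.

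The consequence is limited. No data are lost, and the primary analysis and sample size are untouched. No sparse-event problem has been shown for other short-term outcomes, such as immediate postoperative complications, so the RR can stay as it is for those.

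**What to change.** Add a sentence to the Statistical analysis section: for persistent trophoblast, report the number and percentage of women affected in each arm and the absolute risk difference with a score-type 95% CI (Newcombe, for example), alongside the RR; state which arm is the reference, and give the RR only where it can be computed. Leave the RR as the measure for the other short-term outcomes.

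The cost is that one sentence. It needs no new data, no more patients and no change to follow-up.

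### The Kaplan-Meier curve planned for repeat EP gives a net risk, higher than the actual probability, because follow-up ends at IVF, tubal surgery and apparently viable IUP

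*Protocol article*

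**What the plan says.** All of this is in the protocol article.

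- **Estimator.** Statistical analysis: "Kaplan-Meier curves are constructed, estimating the cumulative probability of spontaneous IUP and repeat EP over time". No cumulative incidence or competing-risks estimator is named.
- **End of follow-up.** Same section: "In case a spontaneous viable IUP does not occur, follow up ends at the last date of consultation". The sentence then adds IVF and tubal surgery as further points at which follow-up stops. The Primary outcome measure section has a similar rule, again only for women without an IUP. Neither section says what happens to a woman in the repeat-EP curve after a viable IUP.
- **After IVF.** "Spontaneous conceptions that occur after failed IVF treatment will be registered, but these pregnancies will not be considered as endpoint in the analysis".
- **Time not exposed to conception.** "The assessment of fertility status is censored for those periods when women used contraceptives or did not have sexual intercourse".
- **Comparison of arms.** A log-rank test, and a fecundity-type rate ratio "calculated through Cox proportional hazard analysis".
- **Purpose.** The Objective asks whether the fertility gain "outweighs the potential disadvantages of this treatment, i.e. persistent trophoblast and an increased risk for repeat EP".
- **Planning figures.** Sample size: "The IUP rate after salpingectomy is assumed to be 40% after 36 months". An increase of 10 to 15% after salpingostomy is called clinically relevant to offset persistent trophoblast and repeat EP. No repeat-EP rate is given anywhere.

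**The concern.** Kaplan-Meier assumes that a woman censored at a given time would have had the same later hazard of the event as the women still followed. Loss of contact can sometimes be treated that way. Stopping because of IVF, tubal surgery or a viable IUP is different, because it takes the woman out of the repeat-EP curve for good. One minus Kaplan-Meier then answers a hypothetical question: what would the risk of repeat EP be if nobody had IVF, tubal surgery or an IUP first? The plan calls the result a cumulative probability, which a reader will take as the share of women who have a repeat EP.

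The distinction matters because the trial weighs one absolute probability against another: a gain in IUP against the harm of repeat EP. The overstatement grows with the rate of the exits. If salpingostomy raises the IUP rate as hoped, and an IUP ends follow-up, its repeat-EP figure is inflated more than that of salpingectomy.

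**Working it through.** The documents contain no repeat-EP figure, so there is no stated value to reproduce. The check asks how far the planned estimator departs from the actual probability.

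**Inputs from the protocol article**
- Horizon: 36 months (Long term follow-up).
- IUP after salpingectomy: 40% at 36 months (Sample size).
- IUP after salpingostomy: 50% to 55%, reading the 10–15% increase as absolute points.

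**Assumptions**
- True 36-month incidence of repeat EP: 5%, 10% or 15%.
- Constant cause-specific hazards.
- A viable IUP ends follow-up for repeat EP; other exits are set aside at first.

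**Formulas.** Let *p* be the true incidence of repeat EP and *q* that of IUP, both at 36 months.
- Total cumulative hazard: H = −ln(1 − p − q)
- Share due to repeat EP: H_EP = H × p/(p + q)
- Displayed by one minus Kaplan-Meier: 1 − exp(−H_EP)

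**Repeat EP truly 10% in both arms**
- IUP 40%: H = −ln(0.50) = 0.6931; H_EP = 0.6931 × 0.10/0.50 = 0.1386; displayed 12.9%.
- IUP 55%: H = −ln(0.35) = 1.0498; H_EP = 1.0498 × 0.10/0.65 = 0.1615; displayed 14.9%.
- Difference displayed: 2.0 points, where the actual probabilities are equal.

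**Displayed value (factor over the true value)**

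| True repeat EP | IUP 40% | IUP 50% | IUP 55% |
|---|---|---|---|
| 5% | 6.4% (1.29) | 7.0% (1.40) | 7.4% (1.47) |
| 10% | 12.9% (1.29) | 14.2% (1.42) | 14.9% (1.49) |
| 15% | 19.6% (1.30) | 21.5% (1.43) | 22.7% (1.52) |

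**Simulation.** 400,000 women, IUP 50%, repeat EP 8%. Censoring at IUP gives 11.3%. Keeping women with an IUP in the risk set to 36 months gives 8.0%, the true value. The excess therefore comes from censoring.

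**If IVF and tubal surgery are the only exits.** The documents give no rate for either. Purely as an illustration, put an assumed exit proportion in place of *q*, with repeat EP at 10%:
- 10% exit: H = −ln(0.80) = 0.2231; H_EP = 0.2231 × 0.10/0.20 = 0.1116; displayed 10.6%.
- 20% exit: H = −ln(0.70) = 0.3567; H_EP = 0.3567 × 0.10/0.30 = 0.1189; displayed 11.2%.

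The direction is the same and the size smaller.

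**The case against.** Four arguments can be made for the plan, and most of each stands.

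**Censoring at IUP is not stated.** The end-of-follow-up rule covers women without an IUP. All women are contacted for 36 months about any pregnancy, and a woman can have an EP after an IUP. This stands as a limit: the table above depends on a reading of the rule. That reading is the natural one, since a rule for what happens when no IUP occurs implies that an IUP is itself an end point, and no separate rule is given for repeat EP. The exits at IVF and tubal surgery are explicit.

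**A net risk is a legitimate target.** Censoring time without exposure suggests interest in risk per time exposed to conception. On that view the 2-point gap is not an artefact: equal 10% incidence at IUP 55% and 40% requires a repeat-EP hazard 0.1615/0.1386 = 1.165 times higher after salpingostomy, and the curve displays it. This too stands, but only for a curve labelled as a net probability. The plan does not label it so, and a net risk is not the actual share of women harmed.

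**The tests are unaffected.** A reader might infer that the comparison of arms is biased. The documents do not support that: the log-rank test and Cox ratio still address the cause-specific hazard.

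**A joint model would do harm.** A reader might infer that IUP and repeat EP should be made mutually competing. A woman can have a spontaneous viable IUP after a repeat EP, and the primary outcome definition does not exclude it. Ending IUP follow-up at every repeat EP would lose such pregnancies.

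It is also tempting to say that the curve keeps women at risk after IUP, IVF or surgery. For IVF and surgery the text says the reverse. Had the women been kept in the risk set, the simulation shows no overstatement.

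**Conclusion.** The point holds for the repeat-EP curve and its label. The planned estimate is a net risk that exceeds the actual probability of repeat EP, and by more in the arm with more IUPs if an IUP ends follow-up. The direction follows from the estimator. The factor of about 1.3 to 1.5 rests on constant hazards, on censoring at IUP, on IUP rates of 40% to 55%, and on assumed repeat-EP rates of 5% to 15%. If only IVF and tubal surgery end follow-up, the excess comes from those exits alone and the documents do not allow it to be sized.

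Repeat EP is a secondary outcome, and neither the primary analysis nor the planned tests are at fault. The change is still worth making, because the stated objective sets this harm against an absolute gain in IUP.

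**What to change.** For repeat EP only:

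1. State whether follow-up for repeat EP ends at a viable spontaneous IUP.
2. Report the Aalen-Johansen cumulative incidence by arm. Treat the events that end follow-up as competing events: IVF, tubal surgery and, if it applies, viable IUP. Give the 36-month absolute difference with its 95% CI.
3. Say how periods without exposure to conception enter this estimate, so that the time scale is clear.
4. If a Kaplan-Meier curve for repeat EP is kept, label it as a net probability per time exposed to conception.
5. Keep the log-rank test and the Cox ratio, described as cause-specific comparisons.

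Leave the primary IUP analysis as planned. Do not make repeat EP an event that ends follow-up for IUP.

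The cost is a few sentences and a small extra analysis in standard software, with no new data. The drawback is that readers will meet two differently defined curves, and the report must explain the difference.

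### Censoring the primary outcome at IVF or any tubal surgery does not match the outcome definition, is plausibly informative, and makes the Kaplan-Meier curves overstate the actual chance of spontaneous pregnancy

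*Protocol article*

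**What the plan says.** The protocol article states the end of follow-up for the primary outcome twice, and differently.

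- Under Primary outcome measure: "The primary outcome measure is the time to the occurrence of a spontaneous viable IUP", and "If an IUP does not occur, follow-up ends on the day of the last consultation". IVF and tubal surgery are not mentioned.
- Under Statistical analysis: "follow up ends at the last date of consultation, or at the moment when either IVF or tubal surgery is performed". It adds: "Spontaneous conceptions that occur after failed IVF treatment will be registered, but these pregnancies will not be considered as endpoint in the analysis".

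The estimators are fixed in the same section: "Kaplan-Meier curves are constructed, estimating the cumulative probability of spontaneous IUP and repeat EP over time", a log-rank test, and a treatment difference "expressed as a FRR with 95% confidence interval, calculated through Cox proportional hazard analysis". The abstract states that "The analysis will be performed according to the intention to treat principle", and the Statistical analysis section repeats this. The abstract describes the cost-effectiveness analysis as "including IVF treatment whenever a spontaneous pregnancy does not occur", which ties IVF to not having conceived spontaneously. The term tubal surgery is not limited to any indication.

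**The concern.** Kaplan-Meier and Cox methods treat a censored woman as having the same future chance of the event as comparable women still under observation. Neither censoring event fits that easily.

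**IVF.** Women move to IVF largely because spontaneous conception is not happening, so those censored are likely to be the less fertile. The operating team knows the allocation, and referral may depend on whether one tube or two remain.

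**Tubal surgery.** Read as written, it covers re-operation for repeat ectopic pregnancy or persistent trophoblast. The Objective names these as the drawbacks of salpingostomy to be weighed against its fertility benefit. A woman re-operated for one of them leaves the primary analysis as if her prospects were unchanged, so the effect of the complication on later fertility is lost from the primary comparison.

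At stake are the meaning of the reported cumulative pregnancy rates and, under some conditions, the between-arm ratio.

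**Working it through.** **1. The two sections applied to one woman.** She has failed IVF, then conceives spontaneously, and the pregnancy is viable at 12 weeks or more.

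| Section | End of follow-up | Her pregnancy |
|---|---|---|
| Primary outcome measure | Last consultation, had no IUP occurred | Meets the definition |
| Statistical analysis | Start of IVF | Registered, not an endpoint |

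The censoring date and the event status both differ. This step needs no assumption.

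**2. Gap between the curve and the cumulative incidence within one arm.** Input from Sample size: 40% IUP at 36 months after salpingectomy, taken here as the Kaplan-Meier value. The article gives no IVF rate, so the IVF hazard *h* is assumed. Hazards are constant and independent.

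- IUP hazard: λ = −ln(0.6)/3 = 0.170 per year. With *h* = 0 this returns the article's 40%.
- Cumulative incidence of IUP before IVF at 3 years: λ/(λ+h) × [1 − exp(−3(λ+h))]. The proportion starting IVF has *h* in place of λ in the numerator.

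| h per year | Start IVF | Kaplan-Meier | Cumulative incidence | Gap (points) |
|---|---|---|---|---|
| 0.05 | 11% | 40% | 37.4% | 2.6 |
| 0.10 | 21% | 40% | 35.0% | 5.0 |
| 0.15 | 29% | 40% | 32.8% | 7.2 |
| 0.20 | 36% | 40% | 30.8% | 9.2 |

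Because IVF is independent of fecundity here, the gap is a difference in what is estimated. Kaplan-Meier gives the chance if IVF did not exist; cumulative incidence gives the chance of a spontaneous IUP before IVF.

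**3. IVF related to fecundity (large simulations).** Assumptions: fecundity varies between women, and IVF is possible from month 12 at a monthly hazard of 0.02 in both arms, or 0.03 after salpingectomy against 0.015 after salpingostomy. The control rate is 40%, or 77%; the latter is what a 1.4-year median implies under a constant hazard (1 − 0.5^(3/1.4) = 77%).

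- *Curves.* Kaplan-Meier lies 1.2 to 4.4 points above even the no-IVF probability at a 40% control rate, and 0.4 to 2.8 points above at 77%. In one scenario with strong dependence and equal IVF rates, the salpingectomy arm shows Kaplan-Meier 43.0%, no-IVF probability 40.0%, full follow-up counting spontaneous IUPs after IVF 39.0%, and cumulative incidence 37.8%.
- *FRR, IVF independent of fecundity:* 1.387 censored against 1.391 without IVF.
- *FRR, IVF dependent but equally frequent:* 1.303 against 1.302, and 1.302 against 1.300.
- *FRR, IVF dependent and twice as frequent after salpingectomy, 40% control rate:* 1.278 against 1.306 (−2.1%), 1.254 against 1.308 (−4.1%), and with no treatment effect 0.951 against 0.996 (−4.5%). At a 77% control rate the shifts are smaller: for example 0.984 against 1.000 (−1.6%) and 1.222 against 1.225 (−0.2%).

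**4. Tubal surgery.** Assume equal fertility before re-operation (λ as above), and re-operation by 36 months in 15% after salpingostomy and 5% after salpingectomy. Later fertility falls to 30-60% of its previous level after salpingostomy and to nil after salpingectomy. The re-operation hazards that give 15% and 5% are 0.070 and 0.022 per year. The true proportion is the step 2 formula plus ∫₀³ h·exp(−(λ+h)t)·[1 − exp(−rλ(3−t))] dt, with *r* the remaining fraction of fertility.

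- Salpingostomy: 37.6% (r = 0.3) to 38.7% (r = 0.6).
- Salpingectomy: 38.8% (r = 0).
- Both censored curves read 40%.

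The rule hides a deficit of 0.1 to 1.2 points in the salpingostomy arm. This favours salpingostomy, whereas the unequal-IVF scenarios in step 3 work against it.

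**The case against.** The rule looks deliberate. The endpoint is spontaneous pregnancy, and the same section also censors periods of contraception or no intercourse, so the target appears to be conception while exposed to that chance. The sentence in the outcome section may be shorthand for the fuller rule. Pregnancies from IVF are a secondary outcome, costs per live birth include IVF, and persistent trophoblast and repeat ectopic pregnancy are secondary outcomes, the latter with its own curve. Persistent trophoblast is treated primarily with methotrexate, and the pairing of IVF with tubal surgery can be read as meaning fertility procedures only. The article condenses a fuller protocol, so the absence of competing-risk or sensitivity analyses from it is no fault.

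Much of this stands. A pre-IVF, cause-specific FRR is interpretable, and it need not be abandoned. Nor is IVF as a competing event clearly better as the primary analysis: with equal fertility, IVF in 21% against 11% gives cumulative incidence of 35.0% against 37.4%, a 2.4-point difference due to IVF uptake alone.

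It does not remove the point. The outcome sentence is complete in itself and gives a different date. The wording on tubal surgery has no limit, and repeat ectopic pregnancy as defined in the article includes cases treated surgically. The criticism rests on the rule as stated, not on what is left out.

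**Conclusion.** The concern holds in a limited form. The two sections disagree on when follow-up ends and on whether a spontaneous viable IUP after IVF counts. The censoring is plausibly informative. The curves overstate the actual cumulative probability of spontaneous IUP: by about 3 to 9 points within an arm against cumulative incidence if 11% to 36% start IVF, and by less against a full follow-up that counts later spontaneous IUPs. These figures rest on assumed IVF rates and constant hazards.

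A reader might infer three stronger things that the document does not support.

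- *That the rule contradicts intention to treat.* No woman leaves her randomised arm. The rule departs only from the fuller sense, in which all outcomes after randomisation count.
- *That the FRR is biased.* For IVF censoring this requires IVF to be both related to fecundity and unequal between arms. The shift is then about 2-5% in the 40% scenarios and under 2% in the 77% examples shown. Unequal IVF and re-operation can act in opposite directions, so the net direction cannot be fixed from the document.
- *That 3 to 9 points can be set against the 10-15% relevance threshold.* The first is a gap within one arm; the second is a difference between arms.

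**What to change.** 1. Do not end follow-up at tubal surgery, at least when it treats a repeat ectopic pregnancy or persistent trophoblast, and count later spontaneous viable IUPs. Define any tubal surgery that still ends follow-up.
2. Keep the IVF-censored log-rank and Cox analysis, described as a cause-specific comparison. Add a prespecified analysis of all women as randomised over 36 months that counts the spontaneous IUPs after failed IVF, which are already registered.
3. Show cumulative incidence with IVF as a competing event beside the Kaplan-Meier curves, and report IVF and re-operation rates by arm so that readers can judge whether the censoring is unequal.
4. Give the Primary outcome measure and Statistical analysis sections the same end of follow-up and the same rule for pregnancies after IVF.

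The cost is wording and a little more analysis. The six-monthly questionnaires already ask about infertility treatment and all pregnancies; the indication for any tubal surgery would have to be available. The reported cumulative rates will be somewhat lower. The choices should be fixed before outcomes by arm are seen.
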